#### 2.4.1. Body Awareness

Many of the men participating in the ‘Wildman Programme’ will have little body awareness and experience problems with their balance. Therefore, in the ‘Wildman Programme’, the participants will be introduced to balance exercises and body and stretching exercises inspired by research on Qigong [48].

Calligraphy health Qigong is an approach that is easy for the participants to engage in and can easily be adapted to the different physical needs in the group and the different nature environments. Qigong exercises are expected to help the participants experience a flow of energy in the whole body and strengthen their body tone and body awareness. In addition, the ‘Wildman Programme’ includes different kinds of outdoor play. These can help the participants strengthen both their physical and mental health, since they increase their heart rate and get their blood circulation activated, while at the same time, they get to play and laugh together [75].

#### 2.4.2. Mind Relaxation And Meditation

During the ‘Wildman Programme’, the participants will also experience body scanning meditations, outdoor sittings, and narrative meditations. The practice will be adapted to the changes in seasons and the weather in Denmark and accordingly, the meditation practice will shift between sitting, standing, walking, laying, and working forms of meditation to keep the participants from getting cold. The narrative meditations are inspired by the mindfulness concept [76] and integrate nature elements and knowledge about our life in nature through time.

In the ‘Wildman Programme’, the participants will learn different breathing exercises that activate the parasympathetic nervous system. The breathing exercises will be repeated in the course and can be done by the participants at home both during and after the course. Breathing exercises are expected to help reduce stress and have a positive physiological impact on the body. Breathing exercises can enhance the sensory experience of nature and can enhance feelings of well-being and reduce stress [42].

#### 2.4.3. Fire Talks, Storytelling, and Community Spirit

An important aim during the ‘Wildman Programme’ is to create positive interactions among the participants. Being together in nature can strengthen positive relationships because social barriers and hierarchy are reduced. Therefore, the participants can experience being more open to others in the group. Research indicate that activities in natural areas often become more spontaneous, since the environment is more unaffected, far less rigid, strict, and organised than in built environments. This in turn can lead participants to be more informal in their contact with each other in natural environments, which in turn can lead to opportunities of spontaneous meetings and networks [77]. This aim relates to the “social” and “culture” spheres according to SET. The ‘Wildman programme’ focuses on creating a team spirit in the group and a common culture where it is allowed to be both vulnerable and resourceful at the same time. The participants should feel safe in each other’s company and be able to tell their own story as well as create a common story in the group [78]. In this aspect, the talks in the group around the bonfire have a significant importance. Evolutionarily, bonfires have offered a kind of refuge and safety from predators [79], and these feelings of safety and refuge can also today make it easier for the participants to be open-minded, to let go, and be present.

One of the goals of the ‘Wildman Programme’ is to create positive social interactions and a remaining network after the programme has ended. Hence, the ‘Wildman Association’ has been established as a club for former participants of the ‘Wildman Programme’, and it is driven by volunteers. On the last day of the course, the participants will meet with the ‘Wildman Association’ consisting of previous participants of the ‘Wildman Programme’, and they get the opportunity to become members of a big network that continues to meet in nature and use some of the techniques they have learned during the ‘Wildman Programme’.

### 2.5. Outcomes

The participants all experience symptoms of stress and reduced quality of life due to their physical or mental health problems. Therefore, the following outcomes have been selected. All primary and secondary outcomes are measured at baseline (T1), post-treatment (T2), and at follow up 6 months post-intervention (T3).

Primary outcome:

The primary outcome is to investigate whether the results from the NBMC approach in the ‘Wildman Programme’ have a significant effect on the participants’ quality of life. The effect will be measured by the following scale:

Self-experienced quality of life: the World Health Organization (WHO)’s brief questionnaire, WHOQOL-BREF [80].

Secondary outcomes:

The secondary outcomes are to investigate whether the ‘Wildman Programme’ has a significant effect on the participants’ level of stress, self-experienced restitution, and job status. The effects will be measured by the following methods:Level of stress: Cohen’s Perceived Stress Scale (PSS) [81].Self-experienced restitution: The Perceived Restorativeness Scale-11 (PRS-11) [82].Job status: Measured by self-reported job status before, post, and 6 months after the intervention.

## 3. Research Design

### 3.1. Flow of Participants

The referred men will be invited to an introductory interview before they can be included in the ‘Wildman Programme’. The sample size in the study will be 104 in total: 52 men will be included in the intervention group and 52 men in the control group will be given treatment as usual (see Figure 2).

The strategy to achieve adequate participants in the study is to establish close cooperation with the health centres and job centres in the two municipalities, which have decided to hire a project leader to coordinate the recruitment to the intervention and control group.

The participants in the intervention group and the control group will be answering a questionnaire at baseline (T1), post-treatment (T2), and at follow up 6 months post-intervention (T3).

The questionnaire will include the following scales:Self-experienced quality of life: WHO’s brief questionnaire, WHOQOL-BREF, which examines four domains in a five-point Likert scale: physical health, mental health, social relationships, and health-related environments, for instance access to medical care. The global quality of life is based on the participants’ scores on the four domains, and they range from 0 to 100, with a high score indicating a high quality of life [80].Level of stress: Cohen’s Perceived Stress Scale, PSS, examines the way you handle stress in daily living on 14 items in a five-point Likert scale [81].Self-experienced restitution: The Perceived Restorativeness Scale-11 (PRS-11) [82] measures with 11 items four different categories of self-experienced restitution related to spontaneous attention: fascination, being away, coherence, and scope. The scale is used for measuring meditation practice and attention training in natural environments.Job status: Measured by self-reported job status before, post, and 6 months after the intervention.

Participants from the intervention group and control group will be contacted by e-mail or by phone if they have not answered the questionnaires. No outcome data will be collected on participants that drop out of the study.

No other nature-based interventions are permitted during the trial.

Data will be securely stored in a locked electronic folder at the University, and data will be analysed in SPSS.

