### 2.3. Intervention

The ‘Wildman Programme’ is led by a nature guide and a health professional (e.g., a physiotherapist, a nurse, or a psychologist) who are experienced in rehabilitation of the included diagnosis and further educated in the nature-based rehabilitation methods. Based on past experiences in the ‘Wildman Programme’, the drop-out rate is expected to be approximately 15% due to the participants’ return to work, hospitalisation, or because the intervention does not suit them.

The intervention has a duration of 12 weeks with one weekly three-hour meeting [24]. In addition, the participants are given homework such as breathing exercises and meditation techniques for around 15 min a day, and they should give themselves breaks during the week by spending time in a self-selected supportive environment in nature in their home area. There are 10–18 participating men in each group of the ‘Wildman Programme’.

The intervention has a permanent chronological structure, which is the same every time the intervention groups meet, but the intervention elements are adjusted accordingly to seasons and weather conditions.

The ‘Wildman Programme’ is described as a ‘Nature–Body–Mind–Community’ (NBMC) approach focusing on nature experiences, body awareness training, attention training, and supporting community spirit explored in the group at base camp and in five other nature environments with different nature qualities.

The NBMC approach has been developed in a pilot project during the period 2014–2018 [64,65]. The ‘Wildman Programme’ consists of the following main elements: (1) Nature environments and nature experiences, (2) Body awareness, (3) Mind relaxation and meditation, and (4) Fire talks, storytelling, and community spirit. In nature, the participants in the ‘Wildman Programme’ will experience bonfires, storytelling, meditation, breathing exercises, and sensory perceptions to reconnect with nature. They listen to the birds, the wind, and the sounds of the creek, and they feel the soil and the leaves and bark on the trees. They lay on their back on the ground, looking up in the treetops, seeing the shades and colours of light and the motion made by the wind; they lie totally quiet and just are in soft fascination [16,32,70,71].

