### 3.2. Statistical Analysis

As we are dealing with a mixed group of participants, the power calculation will be based on an estimate of the medium value (*M*) and the standard deviation (*SD*). Based on population standards for men with low measures on the WHOQOL-BREF scale, the following medium value and standard deviation are estimated: *M* = 57.0, *SD* = 18.0 [63]. According to the population standards for men [83], a 20% improvement equals a change from a low global quality of life to a high global quality of life. In the light of our previous experiences with the courses and the results obtained, a medium size effect can be expected when it comes to self-reported quality of life measured with WHOQOL-BREF (Cohens d = 0.50). A t-test power calculation made by the GPower 3.1 [84] shows that there must be a total of 104 participants to obtain a medium effect on the WHOQOL-BREF (Cohens d = 0.60), by setting the significance level to 5%, the power to 80%, and the expected drop out by the 6 months’ follow up to 15%.

Data from the pilot project showed an improvement in the quality of life for the target group in relation to the mean value and standoffs.

The results of the study will be analysed according to the intention-to-treat perspective. Primary and secondary outcomes at baseline, after end of treatment, will be analysed, and again at a six months’ follow-up applying linear mixed-effects models. Missing data will be dealt with by the maximum likelihood method, as this method is regarded as the optimal method for handling missing data caused by drop out [85].

The effect of the treatment on the global quality of life mediated by the perceived restrictiveness scale is also examined by the Preacher and Hayes macro process for SPSS. The method is based on the maximum likelihood estimation and bootstrap [86].

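### Outcome collection stops at drop-out although the analysis is by intention to treat, and one stated cause of drop-out, return to work, is part of a secondary outcome

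*Protocol article*

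**What the plan says.** Four statements in the protocol article bear on this point.

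- **Section 3.1, Flow of Participants.** Men in both groups "will be contacted by e-mail or by phone if they have not answered the questionnaires". The next sentence sets the limit: "No outcome data will be collected on participants that drop out of the study".
- **Section 3.2, Statistical Analysis.** "The results of the study will be analysed according to the intention-to-treat perspective", using linear mixed-effects models. Maximum likelihood is chosen because "this method is regarded as the optimal method for handling missing data caused by drop out". The sample size allows for 15% drop-out by the six-month follow-up.
- **Section 2.3, Intervention.** Drop-out from the Wildman Programme is also put at about 15%, and is attributed to "return to work, hospitalisation, or because the intervention does not suit them".
- **Section 2.5, Outcomes.** Job status, self-reported at T1, T2 and T3, is a secondary outcome. WHOQOL-BREF is the primary outcome, and perceived stress is another secondary outcome.

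**The concern.** An intention-to-treat analysis needs outcomes to be sought from every included man, whether or not he continues with what he was offered. The rule in section 3.1 does the opposite. It is a positive instruction about data collection, not a detail left to an analysis plan, and no later analysis can recover questionnaires that were never sent.

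The article's own reasons for drop-out make the loss likely to be informative. A man who leaves because he is back at work has reached a favourable value of job status, and that is why the value goes missing. Hospitalisation and finding the programme unsuitable are not outcomes of the study, but they plausibly go with worse quality of life and more stress. Maximum likelihood removes bias from drop-out only when, given the scores already observed, leaving does not depend on the unseen ones. The stated reasons make that doubtful, and a man who leaves before T2 has only his T1 score to inform the model.

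At stake are the job-status comparison and, to a lesser degree, the primary quality-of-life comparison. The study is not randomised, so it already has to argue for comparable groups. This second source of bias is avoidable.

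**Working it through.** **Inputs from the article:** 52 men per arm; drop-out 15%; SD 18.0; d = 0.60 in the power calculation; alpha 5%; power 80%.

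**Assumptions, not in the article:** true return-to-work rate 20–40%; drop-outs differing by 9 or 18 WHOQOL-BREF points (0.5 or 1 SD) from the model's prediction; correlation between visits 0.5–0.7.

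**1. The plan's sample size.** Two-sided, normal approximation: n per arm = 2 × (1.96 + 0.84)² / 0.60² = 43.6, rounded up to 44, so 88 in total. 88 / 0.85 = 103.5, rounded up to 104. The stated total reproduces. It rests on d = 0.60, so the powered effect is 0.60 × 18 = 10.8 points.

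**2. Men affected.** 0.15 × 52 = 7.8, about 8 per arm.

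**3. Job status.** Let p be the true return-to-work rate in an arm and s the share of drop-outs who returned to work. Among men with data:

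observed rate = (p − 0.15 s) / 0.85

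| True p | s = 0 | s = 1/3 | s = 2/3 | s = 1 |
|---|---|---|---|---|
| 20% | 23.5% (+3.5) | 17.6% (−2.4) | 11.8% (−8.2) | 5.9% (−14.1) |
| 30% | 35.3% (+5.3) | 29.4% (−0.6) | 23.5% (−6.5) | 17.6% (−12.4) |
| 40% | 47.1% (+7.1) | 41.2% (+1.2) | 35.3% (−4.7) | 29.4% (−10.6) |

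Errors in brackets are percentage points. The error is zero only when s = p, that is, when drop-outs return to work at the same rate as everyone else.

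**4. WHOQOL-BREF, simple bound.** Shift in arm mean = share missing × difference between drop-outs and the model's prediction for them.

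- 9 points: 0.15 × 9 = 1.35, and 1.35 / 10.8 = 12.5%.
- 18 points: 0.15 × 18 = 2.7, and 2.7 / 10.8 = 25%.

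The sign depends on who leaves. Similar losses in both arms would partly cancel in the comparison.

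**5. WHOQOL-BREF, simulation of three visits** (SD 18, 15% of one arm leaving; bias in points, absolute value):

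| What drives leaving | Maximum likelihood, T2 | Maximum likelihood, T3 | Completers only, T2 | Completers only, T3 |
|---|---|---|---|---|
| Unseen T2 score, log odds ratio 1 per SD | 1.3–1.9 | 0.5–0.6 | about 2.4 | 1.2–1.7 |
| Unseen T2 score, most extreme 15% leave | 3.1–4.1 | 1.3–1.4 | 4.9–5.0 | 2.4–3.5 |
| Baseline score only | about 0 | about 0 | 2.5–3.5 | 2.5–3.5 |

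Maximum likelihood therefore does better than a completer analysis in every case. It is unbiased when leaving depends only on observed scores, and biased when it depends on the unseen ones.

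**The case against.** The best reply is that section 2.3 speaks of leaving the programme and section 3.1 of leaving the study. On that reading, a man who stops attending is still in the study and gets the e-mail and phone reminders. The article does not exclude this, but neither does it say so. It uses one term and one figure, 15%, for both events, and nowhere states that a man who stops attending still completes T2 and T3. Staff could reasonably apply the rule to men who have only left the course, so the wording needs changing on either reading.

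Four stronger readings are tempting and are not supported.

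- *That the result is a completer analysis.* It is not. The mixed model keeps T1 data, and T2 data for men who leave later, and this reduces the bias.
- *That loss must differ between arms because usual care has nothing to drop out of.* Section 2.2 lists physiotherapy, fitness training, mindfulness courses and rehabilitation programmes for the control group, and the sample size applies 15% to the whole study. Reasons for drop-out are given for the programme only, so differential loss is plausible but not shown.
- *That maximum likelihood must fail.* If leaving depends only on scores already observed, its bias is about zero. The difficulty is that uncollected data cannot show whether this is so.
- *That the share of uncounted returners to work equals the bias.* Drop-outs also leave the denominator. With p = 30% and half of the drop-outs back at work, (0.30 − 0.075) / 0.85 = 26.5%, an error of 3.5 points, although 7.5% of the arm are uncounted successes.

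It is also fair to say that a sensitivity analysis for informative drop-out may sit in a statistical analysis plan that is not shown. Its absence here is not counted as a fault.

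**Conclusion.** The point stands. The data-collection rule in section 3.1 conflicts with the intention-to-treat commitment in section 3.2, and the causes of drop-out in section 2.3 make informative missingness likely. Job status is the clearest case, because the outcome itself can cause the missing value. Quality of life and stress after drop-out would rest on a missing-at-random assumption that cannot be tested.

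The sizes rest on the assumptions stated, not on figures in the article. For job status the error in an arm runs from about 14 percentage points too low to 7 too high. For WHOQOL-BREF the shift in an arm mean is 1.35–2.7 points under the simple bound, or 12.5–25% of the powered 10.8. It could be near zero if leaving depends only on observed scores, or 3.1–4.1 points at T2 in the extreme simulated case. Return to work removes good outcomes, while hospitalisation and dissatisfaction probably remove poor ones, so the direction cannot be stated in advance. The change should be made before follow-up begins, because the loss cannot be undone afterwards.

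**What to change.** Replace the sentence in section 3.1 with wording such as:

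> Men who stop attending the programme or TAU remain in the study. T2 and T3 questionnaires, and job status as a minimum, are sought from them by the same e-mail and phone reminders. Collection stops only if a man withdraws from data collection. The reason for stopping is recorded.

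Sections 2.3 and 3.2 should then use separate terms for leaving the programme and for missing outcome data, and say to which of these the 15% applies.

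Optionally, add a sensitivity analysis that shifts the missing values up and down, in either arm, and report the shift at which the conclusion changes. It should run in both directions, since the stated reasons for drop-out point both ways.

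The cost is further contact with about 8 men per arm through a reminder procedure that already exists, and a few lines of text. The sample size of 104 is unchanged.

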### 3.2. Statistical Analysis

As we are dealing with a mixed group of participants, the power calculation will be based on an estimate of the medium value (*M*) and the standard deviation (*SD*). Based on population standards for men with low measures on the WHOQOL-BREF scale, the following medium value and standard deviation are estimated: *M* = 57.0, *SD* = 18.0 [63]. According to the population standards for men [83], a 20% improvement equals a change from a low global quality of life to a high global quality of life. In the light of our previous experiences with the courses and the results obtained, a medium size effect can be expected when it comes to self-reported quality of life measured with WHOQOL-BREF (Cohens d = 0.50). A t-test power calculation made by the GPower 3.1 [84] shows that there must be a total of 104 participants to obtain a medium effect on the WHOQOL-BREF (Cohens d = 0.60), by setting the significance level to 5%, the power to 80%, and the expected drop out by the 6 months’ follow up to 15%.

Data from the pilot project showed an improvement in the quality of life for the target group in relation to the mean value and standoffs.

The results of the study will be analysed according to the intention-to-treat perspective. Primary and secondary outcomes at baseline, after end of treatment, will be analysed, and again at a six months’ follow-up applying linear mixed-effects models. Missing data will be dealt with by the maximum likelihood method, as this method is regarded as the optimal method for handling missing data caused by drop out [85].

The effect of the treatment on the global quality of life mediated by the perceived restrictiveness scale is also examined by the Preacher and Hayes macro process for SPSS. The method is based on the maximum likelihood estimation and bootstrap [86].

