### 1.3. Aim

The aim of the present study is to investigate the effect of a nature-based intervention ‘The Wildman Programme’ on quality of life and symptoms of stress among men with long-term health problems compared to men receiving treatment as usual. A further aim is to investigate which natural environments in rural areas work best as supportive environments in rehabilitation. The purpose of this study protocol is to inform about the study and how it is intended to be conducted. Moreover, through the review process, the design and focus of the study can be improved.

Our expectation is that nature-based rehabilitation is suitable for men with depression and stress or long-term illnesses that can lead to depression and stress, and that the nature-based ‘Wildman Programme’ accordingly can help men with a wide variety of chronic illnesses.

Thus, we expect that the participants receiving the intervention will first and foremost experience a significant improvement in their quality of life measured by the World Health Organization Quality of Life Instruments (WHOQOL-BREF) scale [63] corresponding to a 20% improvement. WHOQOL-BREF is an abbreviated generic Quality of Life Scale developed through the World Health Organization.

Furthermore, we assume significant improvements in the other secondary effect outcomes (symptoms of stress, self-experienced restitution, and return to job) compared to the participants receiving treatment as usual (TAU). As far as we know, this type of intervention or research has never been conducted before.

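### Section 3.2 expects d = 0.50 but sizes the trial for d = 0.60, and section 1.3 implies about 0.63; 104 men give about 64%, 80% or 84% power depending on which is meant

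*Protocol article*

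**What the plan says.** Section 3.2 (Statistical Analysis) takes a WHOQOL-BREF mean of 57.0 and an SD of 18.0. Citing experience from previous courses, it then says that "a medium size effect can be expected when it comes to self-reported quality of life measured with WHOQOL-BREF (Cohens d = 0.50"). The next sentence gives the sample size: "there must be a total of 104 participants to obtain a medium effect on the WHOQOL-BREF (Cohens d = 0.60"). The tool is named, "A t-test power calculation made by the GPower 3.1", and the settings follow, "by setting the significance level to 5%, the power to 80"%, with 15% drop-out by the six-month follow-up. Both effect sizes are called medium.

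Section 1.3 (Aim) states the expectation for the same outcome differently, as a gain in quality of life "corresponding to a 20% improvement". Sections 2.2 and 3.1 split the total into 52 men per group; 2.2 gives 104 as a minimum.

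**The concern.** Two adjacent sentences give different effect sizes for one primary outcome, and nothing explains the step from the first to the second. A trial may be powered for a difference other than the one expected, for instance a smallest worthwhile difference, but the article does not say that it does so. Here the design value lies above the forecast drawn from the sponsor's own courses, so power at the forecast is below the stated 80%.

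At stake is how a non-significant result is read. Sections 4 and 4.2 tie the findings to possible use of the programme in Danish municipalities. A reader who takes 80% as the power for the effect forecast in 3.2 would give a null result more weight than the design supports.

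**Working it through.** **Inputs.** From 3.2: d = 0.50 expected, d = 0.60 used, alpha 5%, power 80%, loss 15%, mean 57.0, SD 18.0, t-test. From 2.2 and 3.1: 52 per arm. From 1.3: 20% improvement. Whether the test is one- or two-sided is not stated; two-sided is assumed and checked in step 5.

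**1. The three effects on one scale** (points = d × SD; the 20% is read as relative to the estimated mean)

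| Source | Points | % of 57.0 | d |
|---|---|---|---|
| 3.2, expected | 0.50 × 18 = 9.0 | 9.0/57 = 15.8% | 0.50 |
| 3.2, sample size | 0.60 × 18 = 10.8 | 10.8/57 = 18.9% | 0.60 |
| 1.3, aim | 0.20 × 57 = 11.4 | 20% | 11.4/18 = 0.63 |

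**2. Reproducing 104.** For a two-sample t-test (noncentral t, two-sided 5%, 80% power, equal arms), d = 0.60 needs 44.6, so 45 per arm and 90 in total.
- Multiplying for loss: 90 × 1.15 = 103.5, so 104.
- Dividing by the retained fraction: 90/0.85 = 105.9, so 106.
- Normal approximation: n = 2(1.960 + 0.842)²/0.60² = 43.6, so 44 per arm; 88/0.85 = 103.5, so 104.

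The stated total is therefore reproduced at d = 0.60.

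**3. The same calculation at d = 0.50.** This needs 63.8, so 64 per arm and 128 in total; 128/0.85 = 150.6, so 151 men (148 with × 1.15). The 104 cannot come from d = 0.50 with these settings.

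**4. Power of the planned size.** After 15% loss, 52 × 0.85 = 44.2, so 44 per arm. The noncentrality is d × √(n/2), with √(44/2) = 4.690 and 86 degrees of freedom.

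| d | Noncentrality, 44 per arm | Power, 44 per arm | Power, 52 per arm (no loss) |
|---|---|---|---|
| 0.50 | 2.345 | 64.0% | 71.4% |
| 0.60 | 2.814 | 79.5% | 85.8% |
| 0.63 | 2.970 | 83.6% | 89.2% |

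With 44 per arm, exactly 80% power is reached at d = 0.604, or 0.604 × 18 = 10.9 points.

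**5. One-sided check.** At d = 0.60 a one-sided 5% test needs 36 per arm, or 72/0.85 = 84.7, so 85 men, which does not reproduce 104. At d = 0.50 with 44 per arm it gives 75%, still below 80%. A one-sided test at d = 0.50 with no loss needs 102 men, but that contradicts both the stated d = 0.60 and the stated 15% allowance.

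**The case against.** The strongest reply is that the article attaches 80% to d = 0.60, where it is right, and nowhere claims 80% at d = 0.50. That stands. A reader might infer that the stated power is miscalculated; it is not. The inputs disagree, while the arithmetic from the chosen input is sound to within rounding.

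A second reply is that 0.50 is not the only stated expectation. The 20% in 1.3 gives d of about 0.63 and 84% power, so the design value lies between two expectations. This also stands, and it means that 64% alone would be a selective summary. It does not remove the problem: 3.2 does not derive 0.60 from the 20%, and the two do not match.

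A third reply is that the planned analysis is a linear mixed model over three time points, not a t-test, and may have more power. That is possible. The article gives no correlation between time points, so the gain cannot be quantified. Gains from baseline adjustment usually assume groups balanced at baseline, which section 4.1 says this non-randomised design cannot assure.

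A reader might also infer that losses after the end of treatment are ignored, because 2.3 uses the same figure ("the drop-out rate is expected to be approximately 15"%). The documents do not show this. Section 2.3 gives no time window, and 3.2 words its 15% as cumulative loss up to the six-month follow-up. Nor do they give a basis for assuming a higher loss.

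**Conclusion.** The point holds as an inconsistency in the only sample-size justification given. Three effect sizes stand for one primary outcome (0.50, 0.60 and about 0.63), and 104 men give about 64%, 79.5% and 84% power respectively. If the forecast in 3.2 is right, the chance of missing the effect is about 36% by the method used for sizing (100% − 64%), against the 20% that a reader would take from the text.

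These figures assume a two-sided t-test, equal arms, 15% loss in each arm and an SD of 18. The 0.63 also assumes that the 20% is relative to the mean of 57.0 and is meant as a difference from treatment as usual. Section 1.3 words it as a gain among men receiving the programme, although the aim in the same section is comparative.

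It might be inferred that the trial must enrol 151 men. That follows only if d = 0.50 is the intended target, and the documents do not settle which value is.

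**What to change.** State one target: the between-group difference against treatment as usual in global WHOQOL-BREF points, with its SD and the resulting d. Use it in both 1.3 and 3.2, and say why it was chosen. If the target stays above the effect expected from earlier courses, say so openly.

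Restate the power along these lines: *52 men per arm, 44 after 15% loss, give about 80% power for d of about 0.60 (about 10.9 points) and about 64% for d = 0.50, by a two-sided 5% t-test.* Add that the planned mixed model may gain some power, depending on a correlation between time points that has not been specified.

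The cost is rewording two sections and accepting a less favourable stated power. No extra men are needed for this correction.

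### Leaving the programme is not separated from leaving the study, so men who stop attending, some because they returned to work, may go unmeasured at T2 and T3

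*Protocol article*

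**What the plan says.** Four parts of the protocol article bear on this.

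- **Section 2.3 (Intervention).** From experience with earlier courses, "the drop-out rate is expected to be approximately 15" per cent. The reasons given are return to work, hospitalisation, and the intervention not suiting the man. No time point is attached.
- **Section 3.1 (Flow of Participants).** Men in either group who have not answered are contacted by e-mail or phone. Then: "No outcome data will be collected on participants that drop out of the study".
- **Section 3.2 (Statistical Analysis).** The sample-size result reads: "there must be a total of 104 participants to obtain a medium effect on the WHOQOL-BREF (Cohens d = 0.60". Its other inputs are a 5% test, 80% power and a 15% allowance for loss, which the article describes as "the expected drop out by the 6 months", that is, by T3. The total of 104 is split 52 and 52. Analysis is by intention to treat, using linear mixed-effects models with maximum likelihood for missing data.
- **Sections 1.3 and 2.5 (Aim; Outcomes).** Return to job is among the expected benefits. Self-reported job status is a secondary outcome at T1, T2 and T3.

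**The concern.** One figure does two jobs. In Section 2.3 it describes men leaving a course, and one of its reasons, poor fit with the intervention, cannot arise in a control arm. In Section 3.2 it is the whole loss of study participants by six months, in both arms. Nothing says how the first kind of drop-out relates to the second.

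The data-collection rule in Section 3.1 makes this matter. If a man who stops attending is treated as having dropped out of the study, he receives no further questionnaires. Return to work is a named reason for stopping and also part of a secondary outcome, so the plan could stop measuring men because they did well on that outcome. Hospitalisation, also named, points the other way. The resulting gaps would depend on outcome, would be tied to the programme, and would arise in the intervention arm by a route that the control arm lacks. An analysis set reduced in this way is no longer the one that intention to treat calls for.

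**Working it through.** **1. The passages side by side**

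| Question | Section 2.3 | Section 3.1 | Section 3.2 |
|---|---|---|---|
| Drop-out from what? | Reads as the programme | The study | Not stated |
| By when? | Not stated | Not stated | Six-month follow-up |
| Which arm? | Intervention (past courses) | Both | Both (total of 104) |
| Consequence | None stated | No outcome data | Sample size enlarged |

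No passage says that a man who leaves the programme stays in the study, and none says that he leaves it.

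**2. How many men**

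52 x 0.15 = 7.8, so about 8 men in the intervention arm.

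**3. What maximum likelihood can do for them**

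A man who leaves during the 12 weeks and is not measured afterwards has only T1. The mixed model then has no post-baseline value from him. Its estimates are valid if missingness depends only on recorded data. Loss caused by a later return to work or a hospital admission, neither of which is recorded once collection stops, need not meet that condition. A man with T2 but no T3 is better placed, because his T2 value informs the model.

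**4. The plan's own sample size**

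Inputs from Section 3.2: d = 0.60, 5% significance, 80% power, 15% loss. Sidedness is not stated; two-sided reproduces the figure.

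- Normal approximation: n per arm = 2 x (1.960 + 0.842)² / 0.60² = 43.6, so 44 per arm and 88 in total. 88 / 0.85 = 103.5, so 104.
- Two-sample t-test: 45 per arm, 90 in total. 90 / 0.85 = 105.9, so 106.

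The stated 104 is reproduced to within two men.

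**5. Power at six months with 52 per arm**

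Power comes from the noncentral t distribution with noncentrality 0.60 x √(n₁n₂ / (n₁ + n₂)) and n₁ + n₂ − 2 degrees of freedom, two-sided 5%. Here n₁ and n₂ are 52 x (1 − loss) in the intervention and control arms. Only the first row uses the plan's own loss figure for both arms. The other rows are assumptions, because the article gives no separate figure for later loss or for control-arm loss.

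| Loss, intervention / control | n₁ / n₂ | Noncentrality | Power |
|---|---|---|---|
| 15% / 15% | 44.2 / 44.2 | 2.821 | 79.7% |
| 20% / 20% | 41.6 / 41.6 | 2.736 | 77.2% |
| 25% / 25% | 39.0 / 39.0 | 2.650 | 74.4% |
| 15% / 10% | 44.2 / 46.8 | 2.861 | 80.8% |
| 15% / 5% | 44.2 / 49.4 | 2.898 | 81.8% |
| 15% / 0% | 44.2 / 52.0 | 2.933 | 82.7% |

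The t-test discards every man without T3. The planned mixed model uses T2 values from men who have them, so the reductions in the second and third rows are upper estimates.

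**The case against.** A reader might go further and infer that the stated 80% power at six months is overstated, because the 15% is used up by the end of the course and nothing is left for the six months after it. The documents do not support that.

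- Section 2.3 gives no time point. Its 15% may be the same six-month total that Section 3.2 states, and power is then 79.7%, in line with the plan.
- Applying the rate to controls could err in the other direction. Section 4.1 (Limitations) argues that the design lowers one source of control-arm loss, and smaller control loss raises power above 80%.
- Chasing non-responders is a way to limit loss. It is not evidence that loss will exceed 15%.

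All of this stands, and it removes the power claim.

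It can also be said that Section 3.1 speaks of dropping out of the study, not of the programme, and that a stated intention-to-treat analysis implies that leavers are followed. That is a possible reading, but it is not written down. If leavers are followed, the programme drop-out rate is not a rate of missing outcomes, and the 15% in Section 3.2 needs another basis. If they are not followed, the bias arises. Under either reading the sections need reconciling.

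Finally, a condensed article may leave detail to a fuller document. Here, however, the rule against collecting data is stated outright, and so is the 15%. The point concerns what the article says, not what it omits.

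**Conclusion.** The point holds as a conflict between the data-collection rule and the intention-to-treat analysis, made possible by one 15% figure that serves for both leaving the programme and loss to follow-up. It affects about 8 of 52 intervention men, and it rests on reading study drop-out as including programme drop-out, which the article permits and does not exclude. The direction and size of any bias cannot be calculated from the documents, since return to work and hospitalisation pull in opposite directions and no split between them is given.

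The sample size reproduces, and no shortfall in power is demonstrated. Power would fall below the 79.7% obtained at the planned loss only if net loss exceeded 15%, which the documents neither state nor rule out. The change is worth making for the sake of bias, whatever the loss turns out to be.

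**What to change.** 1. In Section 3.1, replace the rule on drop-outs: men who stop attending the programme are still sent the T2 and T3 questionnaires, including job status, unless they withdraw consent to data collection. Record the date of and reason for leaving.
2. In Section 2.3, label the 15% as programme drop-out and give the period that it covers.
3. In Section 3.2, state that the 15% means missing outcome data by T3, and give its basis for the control arm. If that basis is uncertain, show power over a short range of loss, as in the table above.

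The cost is a few sentences and two extra mailings for each of about 8 men, some 16 questionnaires. The sample size need not change on this ground.
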